## Results

Currently, women are being recruited for the Expect Study II and a total of 300 women are enrolled. We expect to achieve our goal of 400 participants during April 2018 and postpartum data collection will be finished by March 2019. As a result, first study results are expected in 2019.

## Discussion

This paper describes the protocol of an impact study regarding the implementation of externally validated prediction models combined with risk-based care pathways in obstetric care. Prediction models are becoming increasingly popular in medicine [26]. Although the number of prediction models being published has increased tremendously in recent years, the number of external validation studies remains small [26]. Furthermore, performances of models predicting adverse pregnancy outcomes and the efficacy of preventive interventions for these outcomes are generally documented separately [8,27,28]. Impact studies, describing the effect of using prediction models in daily practice combined with preventive interventions relevant to the estimated risk are nearly non-existent [26]. To the best of our knowledge no impact studies using prediction models in general obstetric practice have been published.

The strengths of our design are the multicenter prospective data collection and the similarity of both cohorts. Recruitment in multiple centers, hospitals and midwife clinics, improves the probability of collecting a representative sample of the obstetric population. This is essential in the Netherlands, since most pregnant women receive antenatal care by midwives at outpatient clinics [29]. Furthermore, optimal measurement of the outcomes is achieved by prospective data collection [30]. Finally, because the two cohorts are kept as similar as possible, we are able to accurately compare the former care-as-usual with the new risk-dependent care.

Some limitations of the design must also be noted. First, since the comparison of secondary outcomes of Expect II with those of Expect I is essentially a before-and-after comparison, time trends in the outcomes can theoretically influence results. In the interpretation of the results, we will take such trends into account, fro exmaple, by looking at trends in the studied outcomes from other regions in the Netherlands.

A second possible limitation of our study is that several outcomes will solely be based on participant questionnaires. Potential recall bias, however, is limited due to the prospective design and the usage of 4 questionnaires at limited intervals. Additionally, questionnaires have been shown to be a valid method of data collection regarding perinatal outcomes and medication exposure during pregnancy [31,32]. In the questionnaires we urge respondents to answer honestly and emphasize that all answers will be treated confidentially and will not influence the care provided by their obstetric health care professional. Furthermore, the additional procedures recommended in the risk-dependent care path are all subject to a shared decision-making process between woman and health care professional. As a result, we expect there is currently no taboo regarding the compliance with given recommendations.

We hypothesize that risk-dependent care results in early detection or prevention of obstetric adverse events and can thus reduce prevalence of neonatal adverse events. However, due to low prevalence rates of approximately 5%, large cohorts (approximately two times 6,800 participants) are necessary in order to achieve sufficient power to detect a reduction of at least 20% [18]. Therefore, the influence of risk-dependent care on the incidence of the neonatal composite outcome will be analyzed using registry data of the region. Moreover, to achieve the desired effects of risk-dependent care, it first needs to be implemented successfully. Thus, implementation should first lead to behavioral changes for both health care professionals and pregnant women.

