**Methods:**

A multicenter prospective cohort study consisting of women who receive risk-dependent care is being performed from April 2017 to April 2018 (Expect Study II). Obstetric risk profiles will be calculated using a Web-based tool, the Expect prediction tool. The primary outcomes are the adherence of health care professionals and compliance of women. Secondary outcomes are patient satisfaction and cost-effectiveness. Outcome measures will be established using Web-based questionnaires. The secondary outcomes of the risk-dependent care cohort (Expect II) will be compared with the outcomes of a similar prospective cohort (Expect I). Women of this similar cohort received former care-as-usual and were prospectively included between July 1, 2013 and December 31, 2015 (Expect I).

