## Methods

### Study Design and Recruitment

In April 2017, the Expect prediction tool, was introduced. The Expect prediction tool was developed to enable individual risk assessment during early pregnancy regarding the risks of PE, GDM, PTB, SGA, and LGA. Validated models selected by the LOC to predict PE and GDM have been incorporated into this tool (unpublished study submitted by [name] et al, January 2018). Risk assessment of spontaneous PTB, SGA and LGA is achieved using the revised LOC guidelines [15]. For nulliparous women, the prediction tool comprises 14 variables concerning anthropometric data, relevant medical history, and family history. For multiparous women the tool enquires 6 more variables, all concerning the women’s obstetric history.

The Expect prediction tool is a Web-based form which calculates the estimated risk profiles. This tool was made available for health care professionals via the Expect study website for implementation in daily obstetric care. Besides the estimated risks of adverse pregnancy outcomes, the tool provides recommendations for tailored antenatal care based on personalized risks (ie, risk-dependent care). In addition, patient information brochures relevant to the patient’s risk profile will be automatically generated. The health care professionals can use this tool during one of the pregnant woman’s antenatal visits before 16 weeks of pregnancy. Using a shared decision approach, the appropriate risk-dependent care path with corresponding preventive measures and check-ups will be selected.

In order to implement risk-dependent care successfully, midwives and gynecologists are encouraged to use the Expect prediction tool by representatives of the LOC. The Expect prediction tool is introduced by email to all obstetric health care professionals in the region. Furthermore, oral presentations will be given at every hospital and at local midwifery meetings. Additionally, the hospitals and midwifery practices are contacted regularly by phone and in person to evaluate the Expect prediction tool.

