The midwives and gynecologists play a central role in enrolling pregnant women into the Expect Study II, by asking women whether they are interested in receiving further information about participating in the Expect Study II. Almost every pregnant woman is eligible for our study. The exclusion criteria are (1) maternal age <18 years, (2) documented multiple pregnancy, and (3) ≥16 weeks of gestation at intake. The eligibility criteria are identical to those of the Expect Study I cohort [13]. Eligible women agreeing to participate are asked to give informed consent and to complete 4 Web-based surveys at enrolment, 24 weeks and 34 weeks of gestation, and 6 weeks after due date.

A personal link to the first online survey will be sent immediately after enrolment. If the survey was not accessed or incomplete, 2 automatic reminders will be sent by email at 3-day intervals for surveys one to three and at 6-day intervals for the postpartum survey. In case of non-response, women will be contacted by phone (provided that a correct phone number is available). If women report PTB at the beginning of survey two or three, they will automatically be redirected to the postpartum survey.

The medical ethical committee of Maastricht University Medical Centre evaluated the study protocol and declared that the study did not fall within the scope of the Dutch Medical Research Involving Human Subjects Act (WMO; METC-17-4-057).

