### Statistical Analysis

Missing values will be handled by imputation. Stochastic regression imputation with predictive mean matching as the imputation model will be used to prevent biased results based on complete case analysis only [19].

Adherence will be calculated by the proportion of women who reported to have received the LOC recommendations regarding adequate vitamin D and calcium intake, preventive aspirin treatment, and OGTT. Answers of participants will be linked to their estimated risk profile based on the Expect prediction tool.

Compliance will be analyzed by calculating the proportion of women who complied with the recommendations received from their health care professional regarding aspirin treatment, OGTT, vitamin D, and calcium intake. Vitamin D is analyzed based on supplement intake and sunlight exposure. Calcium intake is determined by calculating the daily intake from diet and supplement use. Dietary intake will be estimated using answers from a selection of questions from the Dutch National Food Frequency Questionnaire tool [20]. These questions address food products that cumulatively cover >80% of the variance in calcium intake [21]. Total intake of both nutrients will be compared with the recommended intake by the LOC (1000 milligram calcium per day and 10 microgram of vitamin D per day) in order to determine compliance to these recommendations.

The secondary outcomes, patient satisfaction and cost-effectiveness, will be analyzed by comparing Expect Study II with the outcomes of former care-as-usual (Expect Study I). Patient satisfaction scores will be analyzed using multiple linear regression.

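### The satisfaction and cost-effectiveness comparison of Expect II with Expect I may be confounded by which practices are in each cohort, so the claim of an accurate comparison is too strong

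*Protocol article*

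**What the plan says.** The Abstract (Methods) describes Expect II as a cohort "consisting of women who receive risk-dependent care". Under Study Design and Recruitment, use of the tool is optional: "The health care professionals can use this tool during one of the pregnant woman’s antenatal visits before 16 weeks of pregnancy". Uptake is promoted rather than required: "midwives and gynecologists are encouraged to use the Expect prediction tool by representatives of the LOC". The same professionals are the route into the study: "The midwives and gynecologists play a central role in enrolling pregnant women into the Expect Study II". Data Collection adds that each woman's risk profile comes from the tool.

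The comparator, Expect I, enrolled women under former usual care from July 2013 to December 2015. The tool was introduced in April 2017.

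The article states two grounds for similarity. The eligibility criteria are the same (Study Design and Recruitment), and the survey intervals and secondary-outcome questions are similar (Data Collection). From these the Discussion concludes: "because the two cohorts are kept as similar as possible, we are able to accurately compare the former care-as-usual with the new risk-dependent care". The only threat to the between-cohort comparison that it then lists is time trends; reliance on questionnaires is a separate limitation. For the analysis, the article says "Patient satisfaction scores will be analyzed using multiple linear regression", and for costs it names bootstrap and standard sensitivity analyses.

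**The concern.** A woman enters Expect II through two decisions by her professional: to use the tool, and to invite her. No decision about the tool could have shaped Expect I, because the tool did not exist. If professionals who adopt and enrol already differed from the others before April 2017, that difference enters the Expect II minus Expect I contrast and would be credited to risk-dependent care.

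The outcomes are open to this. The Pregnancy and Childbirth Questionnaire asks about satisfaction with the professional during pregnancy and during labor, and about health education, so the identity of the professional bears directly on the score. Visits, tests and admissions, which feed the cost side, plausibly vary by practice too.

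This is a different problem from calendar time. The remedy offered for trends, looking at other Dutch regions, cannot show which practices supplied each cohort. Adjusting for the women's own characteristics would not remove a stable difference between practices either.

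**Working it through.** The article gives no figure for this comparison, so there is none to reproduce. The size can only be illustrated.

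**Inputs**
- Expect II: 400 women (Sample size).
- Expect I: size not stated in the article. Assumed N₁ = 500, 1,000 or 2,000.
- d: difference in mean satisfaction, in SD units, between women of adopting and of other professionals under the same care. Not given; 0.10 SD is assumed.
- a: share of Expect I care delivered by professionals who later adopted. Not given; 1, 0.75, 0.5 and 0 are tried.
- Independent errors, a two-sided 5% test, no true effect of the new care and no time trend.

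**Bias.** Take the mean under usual care as μ for other professionals and μ + d for adopters. With no true effect, the Expect II mean is μ + d and the Expect I mean is a(μ + d) + (1 − a)μ = μ + ad. The expected difference is d − ad = d × (1 − a).

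**Standard error.** SE = √(1/400 + 1/N₁) SD:
- N₁ = 500: √(0.0025 + 0.0020) = 0.067
- N₁ = 1,000: √(0.0025 + 0.0010) = 0.059
- N₁ = 2,000: √(0.0025 + 0.0005) = 0.055

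**False-positive rate.** Φ(−1.96 + bias/SE) + Φ(−1.96 − bias/SE), for d = 0.10 SD:

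| a | Bias (SD) | N₁ = 500 | N₁ = 1,000 | N₁ = 2,000 |
|---|---|---|---|---|
| 1 | 0 | 5% | 5% | 5% |
| 0.75 | 0.025 | 7% | 7% | 7% |
| 0.5 | 0.05 | 12% | 13% | 15% |
| 0 | 0.10 | 32% | 39% | 45% |

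Only the product d × (1 − a) matters. A difference of d = 0.20 SD with a = 0.5 also gives a bias of 0.10 SD, and so the same 32–45%. A larger Expect I cohort raises the rate, because the SE shrinks while the bias stays.

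**The case against.** The strongest reply is that nothing in the article shows the two cohorts to come from different practices. It does not describe who recruited Expect I, and refers to a cited publication for that cohort's criteria. Expect I was also enrolled prospectively and may have drawn on equally willing professionals. The roll-out was regional: the tool was introduced by email to all obstetric professionals, with presentations planned at every hospital, and the consortium represents all hospitals and roughly 80% of the province's midwives (Tailored-Care Paths). If largely the same practices supplied both cohorts, the bias is close to zero. All of this stands, and it is why the point is that the comparison may be confounded, not that it is.

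A second reply also stands in part. The regression may well include centre or type of provider, and a journal article need not list covariates. Their absence is not the fault raised here. The fault is the positive claim of accuracy, drawn from similarities that leave out a selection step the article itself describes.

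A reader might infer more: that false significance is likely, at 32–45% for a 0.10 SD difference or 85–95% for 0.20 SD. Those rates hold only if no Expect I care came from adopters (a = 0), which nothing in the article supports. At a = 0.5 they fall to 12–15% and 32–45%.

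**Conclusion.** The concern holds as a possible bias and an overstated claim. Voluntary tool use, professionals as gatekeepers and a comparator that predates the tool are all stated in the article. Similarity of practices or professionals is not, so the word accurately goes further than the design supports.

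The size is unknown. It is d × (1 − a): nil with full overlap, modest (a false-positive rate of about 7%) for d = 0.10 SD with 75% overlap, and material only with low overlap or a larger d. These figures rest on an assumed Expect I size, an assumed d and independent errors.

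Only patient satisfaction and cost-effectiveness are touched. The primary adherence and compliance proportions use Expect II alone and involve no comparison with Expect I.

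**What to change.** 1. In the Discussion, limit the claim to similarity of women's eligibility and of survey timing and content. Name selection by adopting professionals as a limitation beside time trends.
2. Report how many practices and hospitals, and how many women in each cohort, come from sites that contributed to both.
3. Account for practice in the satisfaction, cost and QALY comparisons. Show an analysis restricted to practices contributing to both cohorts beside the unrestricted one. Which of the two should lead is a matter of judgement and can wait for the overlap figures.
4. Compare Expect I satisfaction between practices that did and did not later enrol in Expect II. This estimates d at practice level from data already collected.

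**Cost.** A practice identifier is needed in both data sets. The restricted analysis loses precision: little where overlap is high and the bias therefore small, more where overlap is low and the correction matters most. Accounting for practice removes stable differences between practices. It does not remove time trends or the selection of individual professionals within a practice, and the text should say so.

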### Tailored-Care Paths

The LOC consists of midwives (n=9), gynecologists (n=9), professionals in maternity care (n=2), researchers (n=3), and an independent chairman. They meet four to five times annually and represent the University medical school, midwifery academy, all hospitals, and roughly 80% (n=90) of the midwives of the province. The midwives and gynecologists of the LOC revised the content of obstetric care. We will briefly describe the most important changes regarding antenatal care compared to former care-as-usual which has been observed during Expect Study I. All women will receive basic antenatal care. In the new tailored care paths, recommendations about calcium and vitamin D supplementation are emphasized for all women and an additional ultrasound for fetal growth assessment at 32 weeks of pregnancy is introduced as part of basic antenatal care.

An overview of the care pathways is provided in Table 1. Additional risk-dependent care for women with a mildly elevated risk of PE comprises the recommendation of preventive aspirin treatment, 80-100 mg aspirin daily from 12 weeks up to 36 weeks of pregnancy. Obstetric care for women with a substantial risk of PE additionally comprises of extended blood tests, blood pressure measurements every 2 weeks from 14 weeks up to 40 weeks of gestation, and 2 additional ultrasounds for fetal growth measurements.

Women with a history of GDM are advised to have an oral glucose tolerance test (OGTT) at 16 and 26 weeks of pregnancy. Women with a mildly elevated risk are advised to have an OGTT at 24 weeks of pregnancy. Furthermore, in both cases, women will receive two additional ultrasounds for fetal growth measurements in addition to basic antenatal care.

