For the economic evaluation, we will use a health care perspective according to the Dutch guidelines for cost calculations [22]. A time horizon of approximately eleven months, from onset of pregnancy up to six weeks post-partum, will be applied. Maternal quality of life will be evaluated using the Euroqol EQ-5D-3L and EuroQol Visual Analogue Scale (EQ VAS) questions which are incorporated in the surveys. The EQ-5D-3L and EQ VAS are standardized questionnaires used worldwide to assess quality of life. Maternal QALYs will be calculated using the corresponding utility scores based on the Dutch population [23,24]. All costs will be expressed as 2017 Euros and if necessary cost prices will be transformed to 2017 Euros using the Dutch Consumer Price Index [25]. Bootstrap- and standard sensitivity analyses will be performed to quantify the uncertainty regarding the cost-effectiveness outcomes.

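### The before-after comparison of costs, QALYs and satisfaction is called accurate, but nothing stated for the economic evaluation deals with case mix, and the time-trend check names no data for the survey outcomes

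*Protocol article*

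**What the plan says.** The Abstract (Methods) gives the two enrolment periods. Women in the comparison cohort "were prospectively included between July 1, 2013 and December 31, 2015 (Expect I"), and the new cohort "is being performed from April 2017 to April 2018 (Expect Study II"). The Discussion acknowledges the limitation, "since the comparison of secondary outcomes of Expect II with those of Expect I is essentially a before-and-after comparison", and says that trends will be taken into account when results are interpreted, for example "by looking at trends in the studied outcomes from other regions in the Netherlands". The paragraph before it lists the comparison as a strength: "because the two cohorts are kept as similar as possible, we are able to accurately compare the former care-as-usual with the new risk-dependent care".

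Statistical Analysis treats the two secondary outcomes differently. For satisfaction: "Patient satisfaction scores will be analyzed using multiple linear regression". For the economic evaluation it sets the perspective, time horizon, utilities and price year, and then: "Bootstrap- and standard sensitivity analyses will be performed to quantify the uncertainty regarding the cost-effectiveness outcomes". No adjustment for differences between the cohorts is stated there.

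Tailored-Care Paths shows that care changed for every woman, not only for those at elevated risk: "recommendations about calcium and vitamin D supplementation are emphasized for all women and an additional ultrasound for fetal growth assessment at 32 weeks" are part of the new paths.

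**The concern.** Two cohorts enrolled about 15 months apart can differ in who joined and in everything else that changed in the meantime. Identical eligibility criteria (Study Design and Recruitment) and similar survey questions and timing (Data Collection) make the measurements comparable. They do not balance case mix or remove drift.

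If the incremental costs and QALYs are simple differences between cohorts, any imbalance or trend enters the cost-effectiveness ratio as if it were impact. The bootstrap interval would be centred on that biased value and would give no sign of the problem. The one safeguard offered against trends comes after estimation and has no identified data for the outcomes that need it most. A reader told that the comparison is accurate would then trust the result more than the design allows.

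**Working it through.** **1. What the stated methods can and cannot capture.** The observed difference between cohorts has three parts:

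observed difference = package effect + case-mix difference + time drift (+ sampling error).

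The bootstrap resamples women within the cohorts, so it reproduces the sampling-error term only. The other two nuisance terms are the same in every resample. The article does not define standard sensitivity analyses. In the usual sense (an assumption) they vary inputs such as unit prices, which does not touch these terms either.

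**2. Whether the trend check has data.**

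| Outcome | Source in the article | Other-region source named? |
|---|---|---|
| Satisfaction | Study surveys two to four (Outcome Measures and Measurement) | No |
| EQ-5D utilities | Study surveys (Statistical Analysis) | No |
| Resource use | Study surveys two to four (Data Collection) | No |
| Incidence of neonatal composite | Registry of the same region (Discussion) | No, but it is a registry outcome, so comparable data could plausibly exist |

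**3. The article's own sample-size figures.** They are not in dispute. For 21% with a half-width of 4 points, n = (1.96/0.04)² × 0.21 × 0.79 = 398.3, which agrees with 400. For 5% versus 4% (two-sided 5% level and 80% power assumed), n = 6,745 per group, which agrees with about 6,800. Neither figure was set for the comparison of costs, QALYs or satisfaction.

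**4. Illustration of size.** Assumed: covariate imbalance d of 0.2 or 0.3 SD; correlation with cost r = 0.3; Expect I size N₁ of 400 to 2,500 (not given in the article); Expect II = 400.

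- Bias = d × r = 0.2 × 0.3 = 0.06 SD, or 0.3 × 0.3 = 0.09 SD.
- SE = √(1/N₁ + 1/400) = 0.071 (N₁ = 400) or 0.054 (N₁ = 2,500).
- Bias/SE at 0.06 SD = 0.85 or 1.1.
- Chance that a nominal 5% test rejects when there is no effect = Φ(−1.96 + bias/SE) + Φ(−1.96 − bias/SE) = 13.6% or 20.0%. At 0.09 SD it is 24.7% or 38.7%.

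**5. Whether adjustment is feasible.** The models were externally validated in Expect I (Introduction), which gave the 30% at elevated pre-eclampsia risk (Sample size). Expect II records each woman's risk profile (Data Collection). The predictors of the validated pre-eclampsia and gestational diabetes models should therefore exist in both cohorts. For preterm birth and for small or large infants the tool uses revised guidelines, and the article does not document those risks for Expect I.

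**6. Contrast by predicted risk.** With elevated-risk share f equal in both cohorts and a common SD, SE(interaction)/SE(overall) = √(1/f + 1/(1−f)). At f = 0.30 this is √(3.33 + 1.43) = 2.18; at 0.40 it is 2.04; at 0.50 it is 2.00. With 400 to 2,000 women assumed in Expect I and 80% power, the detectable difference at f = 0.30 rises from 0.20–0.15 SD to 0.43–0.33 SD.

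**7. A linear month-of-enrolment term beside cohort.** The enrolment periods do not overlap. With uniform enrolment over 30 and 12 months, the cohort means lie about 36 months apart and the within-cohort variances of month are 30²/12 = 75 and 12²/12 = 12. The variance of the cohort effect becomes (1/N₁ + 1/400) + 36²/(75N₁ + 12 × 400).

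- N₁ = 400: 0.0050 + 0.0372 = 0.0422, SE ratio √(0.0422/0.0050) = 2.9.
- N₁ = 2,500: 0.0029 + 0.0067 = 0.0096, SE ratio √(0.0096/0.0029) = 1.8.

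The term would multiply the SE by 1.8 to 2.9 and make the cohort effect an extrapolation across the gap.

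**The case against.** The strongest reply is that this is a journal article. Covariates for a secondary economic comparison are commonly left to a fuller plan, and the article nowhere says that the ratios will be unadjusted. Satisfaction already has a multiple regression. The before-after limitation is disclosed, and other-region trends are only an example. All of this stands, and silence on covariates would not be a finding by itself. It does not rescue the accuracy claim, which is stated outright, nor a trend check that is confined to interpretation and has no named data for the survey outcomes.

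It is also fair to say that the universal changes are part of the new care paths, so their costs and effects belong in the ratio. That stands too. Mixing universal and risk-dependent changes is not an error, provided the result is described as the effect of the package.

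Three stronger readings are tempting, and the document does not support them.

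- A reader might infer that low-risk women form an internal control, so that a cohort-by-risk interaction isolates risk-dependent care. They are not untreated: they receive the new basic care, and some may enter the preterm-birth or small/large-infant pathways in Table 1. The interaction also needs parallel trends across risk groups.
- A reader might take the 14% to 39% rejection rates as the plan's error rate. They rest on assumed imbalance, correlation and Expect I size, and the article plans no hypothesis test of costs.
- A reader might think the neonatal composite depends on the survey cohorts alone. The Discussion assigns the analysis of its incidence to regional registry data.

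**Conclusion.** The concern holds in a limited form. As written, the economic comparison can report case mix or drift as impact, with intervals that reflect neither. The time-trend check cannot be carried out from any source named for satisfaction, EQ-5D or self-reported resource use. The claim that the two kinds of care can be compared accurately goes beyond what the design supports and conflicts with the limitation stated in the next paragraph.

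The amount of bias is unknown, and no imbalance has been shown. The illustration says only that a modest imbalance could be about as large as one standard error. Adherence and compliance, the primary outcomes, are proportions within Expect II and are unaffected. The change is worth making because it reduces bias at little cost, but adjustment for measured predictors will not remove time trends.

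**What to change.** 1. Estimate incremental costs, incremental QALYs and satisfaction from regression models containing cohort and the baseline predictors used by the validated pre-eclampsia and gestational diabetes models in both cohorts. Refit the models within each bootstrap sample. Do not add a linear month-of-enrolment term to the main model.
2. As a sensitivity analysis only, report the cohort contrast by predicted pre-eclampsia/gestational diabetes risk group. State that the interaction estimates the added effect in elevated-risk women, assumes parallel trends across risk groups, removes universal changes that belong in the ratio, and has about twice the SE of the overall contrast.
3. Limit the other-region trend check to outcomes that have such data, such as registry-recorded neonatal outcomes, and name the source.
4. Replace the accuracy claim in the Discussion with: an adjusted before-after estimate of the whole care package, universal plus risk-dependent changes, in which residual time trends cannot be excluded.

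The cost is some extra analysis on data that both cohorts should already hold, and a more cautious conclusion. No new data collection is needed for items 1, 2 and 4; item 3 needs access to any registry used.
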